## Abstract

**Background:**

Heart failure (HF) is an important public health problem, considered a new epidemic with high morbidity and mortality. The progression of HF often determines weight reduction, muscle mass loss, and reduced physical ability. Whey protein supplementation may increase the effects of exercise on strength and muscle mass, in addition to promoting improved endothelial function, body composition and quality of life. However, studies are needed to evaluate its benefits in patients with HF.

**Methods/design:**

This is a double-blind, randomized, placebo-controlled clinical trial in which patients with HF will be randomly allocated to two groups to receive supplementation with whey protein or placebo, associated with supervised exercise, for 12 weeks. The frequency of exercise will be three times a week. The study variables will be evaluated at baseline and 12 weeks. The main outcome will be maintenance of muscle mass and strength. Microvascular reactivity, quality of life, and inflammatory parameters will be evaluated as secondary outcomes.

**Discussion:**

HF is associated with severe loss of muscle mass and strength, directly contributing to exercise intolerance and inability to maintain daily life activities, becoming a strong predictor of reduced quality of life and mortality. The results of this study will add to the evidence base for providing new dietary recommendations.

**Trial registration:**

ClinicalTrials.gov, ID: NCT03142399. Registered on 29 May 2016. Effect of Whey Protein’ Supplementation and Exercise in Patients with Heart Failure (PROT-HF).

**Electronic supplementary material:**

The online version of this article (10.1186/s13063-018-2811-4) contains supplementary material, which is available to authorized users.

## Background

Heart failure (HF) is a clinical syndrome associated with poor quality of life, high utilization of economic resources, largely related to high hospitalization rates, and is a major cause of mortality worldwide [1–3].

Loss of muscle mass is a serious complication that affects a large proportion of patients with HF [4, 5], causing an impact on the physical capacity, quality of life, and survival of these patients. The impairment of cardiac muscle function leads to numerous neurohormonal and metabolic disorders, including an imbalance between anabolic and catabolic processes [6], being a complex scenario in which drug treatments are not available. Two distinct conditions that may be present in this group of patients, and are characterized by loss of skeletal muscle mass, are sarcopenia and cachexia.

Cachexia is a complex syndrome characterized by severe and involuntary muscle mass loss, associated or not with loss of adipose tissue. It is common in chronic diseases, such as cancer and HF, and may even occur in the absence of chronic diseases, since sarcopenia represents a slow and progressive muscle mass loss which comes with aging [7]. The prevalence of sarcopenia varies according to age groups representing 1–2% per year after 50 years, 15% at 65 years, and 50% at 80 years [8].

Regardless of its causes or mechanisms, loss of muscle mass directly contributes to exercise intolerance and impairment of daily life activities, becoming a strong predictor of reduced quality of life and mortality [9–11].

Physical exercise has been shown to be a non-pharmacological, effective, low-cost, and safe therapy that can aid in the treatment of HF, inducing anabolism through the activation or deactivation of molecular pathways essential for muscle synthesis, improving physical capacity and increasing lean mass in those patients with previous depletion [12–15]. Cardiac rehabilitation programs in patients with HF reduce mortality and hospitalization rates and improve functional ability, duration of exercise, and quality of life [16, 17].

It is well established that food consumption is a strong stimulator of muscle protein synthesis [18, 19]. Intake of protein-rich meals in the form of free amino acids [20], milk protein [21], or meat [22] is able to stimulate muscle protein synthesis. This response depends on the amount, and also on the type of protein that is ingested [23]. Whey protein (WP) is a high-quality protein that has shown superiority in enhancing muscle protein synthesis compared with other protein sources in older adults, it is rapidly digested and has a high concentration of leucine [24] that plays an important role in the stimulation of postprandial muscle protein synthesis [25]. Leucine is one of the essential amino acids in the diet. It is capable, like all branched-chain amino acids, of avoiding hepatic alterations due to the lack of L-branched chain aminotransferase in the liver and its ingestion reportedly activates the mTOR pathway in skeletal muscle, contributing to a hypertrophy response [26].

Whey protein has already demonstrated a positive effect on protein synthesis and muscle mass gain [27] when associated with exercise [28, 29], but there are no studies in the academic literature that evaluate its benefits in patients with HF.

Currently, the most promising approach to treat depletion of nutritional status due to the disease appears to be a combination therapy that includes exercise, nutritional counseling, and drug therapy [4, 30], helping to manage symptoms, reducing the number of readmissions, and improving life quality [31].

Thus, the main objective of this study will be to evaluate whether supplementation with WP alone in association with 12-week supervised exercise will be able to preserve muscle mass in patients with New York Heart Association (NYHA) functional class I or II HF. As secondary objectives, an increase in muscle strength, an improvement in endothelial function assessed through microvascular reactivity, improvement in quality of life, and reduction of inflammatory markers will be evaluated.

## Methods/design

### Study design and interventions

This is a double-blind, randomized, placebo-controlled clinical trial in which participants will be followed-up for a 12-week intervention period in which they will undergo supervised exercise through cardiac rehabilitation program participation. Participants will randomly be allocated into two groups to receive supplementation with WP alone or placebo and outcomes will be measured at baseline and upon completion of 12 weeks of study.

For the intervention group will be the supplementation of WP isolate at an amount of 30 g per day, totaling 27 g of protein and 120 kcal per serving. For the placebo group, maltodextrin will be given at an amount of 30 g per day, totaling 30 g of carbohydrates and 120 kcal per serving.

Patients will be instructed to consume supplements daily for 12 weeks, and consumption will be performed immediately after the training session on days of cardiac rehabilitation and on days without training, consumption will be performed at a time defined by the patient.

The study protocol complies with the Standard Protocol Items: Recommendations for Clinical Trials (SPIRIT) guidelines.

### Setting

The study will occur at the National Institute of Cardiology in Rio de Janeiro, Brazil, a reference unit in tertiary-level cardiology treatment linked to the Brazilian Ministry of Health.

### Participants

Patients with a clinical diagnosis of HF, with NYHA functional class I or II, and who have been referred for cardiac rehabilitation by their attending physicians, will be assessed.

### Inclusion criteria

Age ≥ 50 yearsHeart failure functional class I or II NYHAClinical stability (symptoms and medication) for more than 4 weeksEjection fraction ≤ 50%

### Exclusion criteria

Creatinine clearance < 50 ml / min / 1.73 m^2^, impaired hepatic function (alanine aminotransferase > 150 U / l) or decompensated hepatic cirrhosis classified as Child-Pugh grade B or C, atrial fibrillation with heart rate > 100 bpm, allergies to milk proteins, and any osteoarticular impediment preventing physical exercise.

### Additional exclusion criteria

After the initial medical consultation, patients who are unable to understand and perform the study procedures will be excluded.

During the exercise protocol, participants will be under medical supervision to reduce any health risk, and those with decompensated heart disease will be referred to the emergency room of the hospital where the study will be conducted.

### Endpoints

The main outcome will be maintenance of muscle mass and strength. Microvascular reactivity, quality of life, and inflammatory parameters will be evaluated as secondary outcomes.

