### Sample size

Considering a muscle mass gain of 500 g in the intervention group at 12 weeks compared to the placebo group, with a standard deviation (SD) of 409.7 g, 11 patients in each group are required to guarantee 95% confidence and 80% power to the study. The results obtained in a similar study with WP supplementation were used as a reference [33].

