### Statistical analysis

Categorical variables will be presented as frequencies with percentages and will be compared using Fisher’s exact test and the chi-square test. Continuous variables will be presented as mean ± SD or median and interquartile range and will be compared using two-way analysis of variance (ANOVA) or Friedman’s test, whenever appropriate. A logistic regression analysis will be used to identify variables with an independent association with increase of lean muscle mass. A value of *p* < 0.05 will be considered statistically significant in all analyses. Calculations will be performed using the Statistical Package for the Social Sciences (SPSS 21.0 for Windows) program.

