## Discussion

The proposed study is a double-blind, randomized, placebo-controlled clinical trial aimed at investigating the effects of WP supplementation associated with 12 weeks of supervised exercise in maintaining muscle strength in patients with HF. Advanced HF is often associated with severe loss of body weight and especially of muscle mass, and it is an important cause of hospitalization and one of the most important health challenges since its prevalence tends to increase with the aging of the population and the increase in the survival of patients who have suffered acute coronary events. It is an ongoing epidemic problem, resulting in a high socioeconomic cost, represented by the expenditure on medicines, repeated hospitalizations, loss of productivity, early retirement, possible surgeries and, ultimately, the need for heart transplantation. In this sense, it is of great importance to carry out studies that evaluate the possible benefits of new clinical and nutritional interventions for HF patients, favoring the development of new treatment strategies.

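### Muscle strength is part of the main outcome in the Endpoints section but only a secondary objective in the Background, and the sample size and 5% level fit only the Background version

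*Protocol article*

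**What the plan says.** All references are to the Protocol article.

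- **Endpoints** (the abstract's Methods/design paragraph agrees): "The main outcome will be maintenance of muscle mass and strength". Strength is absent from the list that follows: "Microvascular reactivity, quality of life, and inflammatory parameters will be evaluated as secondary outcomes".
- **Background, last paragraph:** the main objective is whether whey protein with "supervised exercise will be able to preserve muscle mass in patients with New York Heart Association (NYHA) functional class I or II HF". Strength then opens the secondary list: "As secondary objectives, an increase in muscle strength".
- **Discussion, first sentence:** the aim is described through "12 weeks of supervised exercise in maintaining muscle strength in patients with HF". Muscle mass is not named in that aim.
- **Sample size:** "Considering a muscle mass gain of 500 g in the intervention group at 12 weeks compared to the placebo group", with an SD of 409.7 g, 95% confidence, 80% power and 11 patients per group. No effect or SD is given for strength.
- **Statistical analysis:** p < 0.05 "will be considered statistically significant in all analyses".

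**The concern.** Strength cannot be both part of the main outcome and a secondary objective. The article supports either reading, and the error rate and power depend on which one applies.

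The trial plans only 22 patients. Once results are known, a report could take mass alone, or mass and strength together, as the primary result and cite the article for it. The Ethics and dissemination section plans to present partial results at congresses during the trial, so comparative data might be seen before the conflict is settled.

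The wording adds a smaller inconsistency. The Endpoints section speaks of maintenance and the Background of preservation, whereas the sample size rests on a gain relative to placebo.

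**Working it through.** **Inputs from the Protocol article.** Difference 500 g, SD 409.7 g, 11 per group, 95% confidence (taken as two-sided alpha 0.05), 80% power (Sample size); p < 0.05 throughout (Statistical analysis).

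**Inputs assumed, because the article does not give them.** Mass-strength correlation 0 to 0.8; strength effect 1.22, 0.8 or 0.5 SD.

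**Step 1: reproduce the stated sample size.** Standardised effect: 500/409.7 = 1.22. Normal approximation: n per group = 2 × [(1.960 + 0.842)/1.2204]² = 10.54, rounded up to 11. The stated figure reproduces.

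Power at n = 11:
- Normal approximation: 1.2204 × √(11/2) = 2.862, and Φ(2.862 − 1.960) = 81.7%.
- Two-sample t-test (20 df): 77.7%. This is the like-for-like baseline for the t-test results below.

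**Step 2: mass alone is primary (Background).** The 11 per group, the 5% level and the 80% power all stand on the normal approximation used for sizing.

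**Step 3: mass and strength, either suffices (one reading of Endpoints).** With independent outcomes the family-wise error is 1 − 0.95² = 9.75%. Simulated pairs of t-tests, 11 per arm, no true effect:

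| Correlation | P(at least one p < 0.05) |
|---|---|
| 0 | 9.7% |
| 0.5 | 9.1% |
| 0.8 | 7.9% |

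**Step 4: mass and strength, both required (the other reading).** The 5% level is then protected, but power drops. Simulated t-tests, 11 per arm, mass effect 1.22 SD:

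| Strength effect | Correlation 0 | 0.5 | 0.8 |
|---|---|---|---|
| 1.22 SD | 60% | 65% | 70% |
| 0.8 SD | 33% | 39% | 42% |
| 0.5 SD | 15% | 19% | 20% |

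Check of the first cell: 0.777 × 0.777 = 0.604.

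The normal approximation, with the equal 1.22 SD effect, gives 67% (correlation 0) to 77% (correlation 0.9), against 81.7% for mass alone. Either method shows a fall.

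**Step 5: size needed if both are required.** With the equal effect and t-tests, 80% joint power needs 15 per group at correlation 0 and about 14 at correlation 0.8. The t-test figure for mass alone is 12 (11.58 rounded up). With a strength effect of 0.8 SD the normal approximation gives 25 to 26 per group.

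**The case against.** **The Discussion is not a third endpoint definition.** A reader might infer three competing primary endpoints. The Discussion sentence is an introductory statement of aim, and the next sentence stresses loss of muscle mass. This objection stands: the sentence only supports the finding of inconsistency. The firm conflict is between Endpoints and abstract on one side and Background on the other.

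**The loss of error control or power is conditional.** A reader might infer that the 5% level or the 80% power is already lost. The article does not support that. If the Background objective governs, and it is the one that matches the sizing, nothing is lost.

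**Part of the gap below 80% comes from the formula.** A t-test at n = 11 gives 77.7% even for mass alone. The fall due to the second outcome must be measured from there. This is correct, and the figures above do so.

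**The joint power rests on an assumed strength effect.** This also stands, which is why a range is shown.

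**A both-or-either rule may sit in an analysis plan that is not shown.** That is fair, and its absence is not the finding. An unseen rule does not remove the conflict, because this article assigns strength two different roles.

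**Within-arm claims.** A reader might take the word maintenance to mean that success could be declared from no loss within one arm. No section proposes this: the design is placebo-controlled and the sizing is a comparison with placebo. The wording is loose, but it is not evidence of a different hypothesis. Nor is the use of p < 0.05 for the other secondary outcomes part of this point.

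**Conclusion.** The point holds as a contradiction in the current text over the role of strength. The sample size figure is not wrong for muscle mass. What is unsettled is whether mass alone is the primary endpoint.

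- **Mass alone governs:** the stated sizing and the 5% level stand.
- **Mass and strength, either suffices:** family-wise error is about 8 to 10% instead of 5%.
- **Mass and strength, both required:** power falls from 78% to about 60 to 70% if strength has the same 1.22 SD effect, 33 to 42% at 0.8 SD, and 15 to 20% at 0.5 SD.

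These ranges assume t-tests, 11 evaluable patients per arm and a mass-strength correlation between 0 and 0.8. The correlation and the strength effects are assumptions.

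**What to change.** Before any comparative data are seen, including at a congress presentation of partial results:

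1. Name one primary endpoint: the between-group difference in change in muscle mass from baseline to week 12. It matches the main objective and the sample size.
2. Make handgrip strength the first secondary endpoint, with a confirmatory test only if the primary succeeds.
3. Align the abstract, Endpoints and Discussion with this, and describe the outcome as change versus placebo rather than maintenance.

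If the sponsor prefers to keep both as co-primary, it should state that both must succeed, give an effect and SD for strength, and restate the power. That route may need more patients.

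**Cost.** The single-primary route is an amendment of wording, reported to the Ethics Committee, with no extra patients. The downside is that strength can no longer be claimed as a primary result. Recruitment is already under way, so the amendment should be dated and its timing relative to any data review recorded.

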### Study procedures

Figure 1 describes all the study steps, from patient recruitment to intervention. Patients will be pre-selected from the waiting list for participation in the cardiac rehabilitation (CR) program. The waiting list consists of patients with HF who were referred to the CR program by their assisting physicians and are waiting to be scheduled. Telephone contact will be made with patients meeting the inclusion criteria, who will be scheduled for consultation with a cardiologist. During consultation, the inclusion criteria will be checked, and the informed consent will be signed. Finally, patients will be randomized and allocated to a study group.

**Fig. 1 Fig1:**
[figure not shown]
Study flowchart

The procedures performed at the beginning of the study will be a cardiopulmonary exercise test (CPET), echocardiogram, microvascular reactivity test, blood collection for biochemical evaluation, handgrip-strength assessment, anthropometric and body composition evaluation, health-related quality of life assessment, and assessment of dietary intake. All initial evaluations will be repeated at 12 weeks.

All staff will be trained in the operation of the equipment for data collection and obtaining written informed consent. Additionally all members of the research team will participate in the work meetings to periodically evaluate the quality of the information collected, in order to minimize errors and ensure the reliability of the data. All the research team will be trained every 6 months during the research period.

Participants will receive a weekly structured telephone interview, with questions addressing side effects (mainly gastrointestinal), symptoms, adherence, and difficulties in carrying out the guidelines provided during the study.

### Randomization and blinding

Randomization will occur in blocks of 2 and will be based on a table of random numbers generated in the online open program Openepi [32]. The random number table will be confidential. The packaging and distribution of the supplements will be performed by personnel not involved in the research. All researchers directly involved in the care and follow-up of the participating patients will not be aware of the supplements taken by the study patients. Unblinding may occur if requested by the assisting physician if a patient suffers clinical destabilization. The supplements will be delivered to the patients in metalized packages, sealed and identified by the name and code of the patient in the study, and it is not possible to identify the supplement as placebo or WP.

### Sample size

Considering a muscle mass gain of 500 g in the intervention group at 12 weeks compared to the placebo group, with a standard deviation (SD) of 409.7 g, 11 patients in each group are required to guarantee 95% confidence and 80% power to the study. The results obtained in a similar study with WP supplementation were used as a reference [33].

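### Eleven patients per group give about 78% power with the planned type of test, not a guaranteed 80%, and any loss lowers it further

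*Protocol article*

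**What the plan says.** The Sample size section sets the effect ("Considering a muscle mass gain of 500 g in the intervention group at 12 weeks compared to the placebo group") and the variability ("with a standard deviation (SD) of 409.7 g"), and concludes that "11 patients in each group are required to guarantee 95% confidence and 80% power to the study". It names no formula, test or sidedness, and it states no allowance for loss. On the origin of the figures it says: "The results obtained in a similar study with WP supplementation were used as a reference". The population of that reference study is not given.

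Three other places bear on the point:
- Randomization and blinding: "Randomization will occur in blocks of 2", which for two groups means equal allocation.
- Statistical analysis: continuous variables are to be compared by two-way ANOVA or Friedman's test.
- Background, on whey protein: "there are no studies in the academic literature that evaluate its benefits in patients with HF".

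**The concern.** With about 20 patients, the large-sample normal formula is slightly optimistic. It treats the SD as known, whereas a t or F test estimates it from few degrees of freedom. A number taken from that formula can fall short of its target power under the test that will be used, and here the text claims a guarantee.

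The normal formula gave 10.54 and was rounded up by less than half a patient, so nothing is held in reserve. The main comparison needs a 12-week body-composition measurement after three supervised sessions a week, so each patient without that measurement costs power directly. The calculation also depends on a single SD, given to a tenth of a gram, with no range around it.

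At stake is how the result is read. Readers of a 22-patient trial will use the stated power to judge what a non-significant result means, so the figure should match the planned test.

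**Working it through.** **Inputs.** From Sample size: difference Δ = 500 g; SD σ = 409.7 g; power 80%; α = 0.05, read from the 95% confidence. From Randomization and blinding: 1:1 allocation. Two assumptions are needed. The test is two-sided, and 409.7 g is the common SD of the quantity compared (the text does not say whether it refers to change or to final value).

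**Step 1: reproduce the plan's figure.** Large-sample normal formula:

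n per group = 2(1.960 + 0.842)² / (Δ/σ)²

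Δ/σ = 500/409.7 = 1.220, and 1.220² ≈ 1.489. So n = 2 × 7.849 / 1.489 = 10.54, rounded up to **11**. This matches the plan. The one-sided version gives 9, which does not match, so two-sided is the reading that fits.

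Power by the same approximation at n = 11:
- Standard error = 409.7 × √(2/11) = 174.7 g
- 500/174.7 = 2.862
- Power = Φ(2.862 − 1.960) = **81.7%**

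**Step 2: use a t-type test.** With two groups and two time points, the group-by-time comparison in an ANOVA is equivalent to a two-sample t-test on change, with 2n − 2 degrees of freedom. Power is the probability that a non-central t variable, with non-centrality δ = Δ / (σ√(2/n)), exceeds the two-sided 5% critical value in absolute size.

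| Evaluable per group | df | Critical t | δ | Power |
|---|---|---|---|---|
| 12 | 22 | 2.074 | 2.989 | 81.5% |
| 11 | 20 | 2.086 | 2.862 | **77.7%** |
| 10 | 18 | 2.101 | 2.729 | 73.3% |
| 9 | 16 | 2.120 | 2.589 | 68.1% |
| 8 | 14 | 2.145 | 2.441 | 62.2% |

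The shortfall at 11 is 80 − 77.7 = 2.3 points, and 12 per group is the smallest number that reaches 80%. Losing one patient in one group only (11 against 10) gives 75.5%. The difference detectable with 80% power is about 515 g at 11 per group, 543 g at 10 and 576 g at 9.

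**Step 3: does the normal formula leave room for loss?** No. At 10 per group its own power is Φ(2.729 − 1.960) = 77.9%, so one loss per group takes even the favourable approximation below 80%.

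**Step 4: sensitivity to the SD.** The document gives no alternative SD, so these values are assumptions, for illustration only. At 11 per group by the t-test: 450 g gives 69.8%, 500 g gives 60.7% and 600 g gives 46.0%.

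**The case against.** The strongest reply is that nothing was miscalculated. The standard formula reproduces 11 exactly, the section names no test, and the t correction adds one patient per group and moves the detectable difference from 500 g to about 515 g, roughly 3%. That is less than the likely uncertainty in the SD. All of this stands, and a reader who inferred an arithmetic error would be wrong. It does not rescue the statement itself: the article plans ANOVA, and on its own inputs that type of test does not reach the power it says is guaranteed.

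Three stronger readings are tempting and are not supported:

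- *The article states that the SD comes from outside heart failure.* It does not. Sample size refers to a similar whey study without naming its population, and Background says no study has evaluated whey's benefits in heart failure. Together they imply an outside source, but neither says so. If Background is right, borrowing an SD was unavoidable, and the source is openly cited.
- *Loss was ignored.* The article states no allowance, but it is a condensed account. The 11 may mean evaluable patients, and a recruitment figure may stand in the full protocol. No loss rate is given, so the rows for 10, 9 and 8 show consequences and are not forecasts.
- *The real power is 46% to 61%.* Those figures rest on SDs of 600 g and 500 g that appear nowhere in the document, and nothing in it shows that the SD in heart failure would be larger.

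Nor does the article say that a null result will be taken as evidence against whey. Moving from 80% to 77.7% would not by itself change such a reading.

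**Conclusion.** The point holds as a modest one. With 500 g, SD 409.7 g, a two-sided 5% t-type test and no loss, 11 per group give 77.7% power against the stated 80%; 12 would be needed. The gap alone is minor. It matters because there is no margin below it: power is about 73% with 10 evaluable patients per group and about 68% with 9.

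The conclusion assumes a two-sided test, the stated SD applied to the quantity analysed, and ANOVA with 20 degrees of freedom for the group comparison. Power was not worked out for Friedman's test, the alternative the article names. The outside origin of the SD is an inference, which supports caution about the word guarantee and nothing stronger.

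**What to change.** Restate the sample size along these lines: 11 evaluable patients per group give about 78% power (two-sided 5% t-test) to detect a 500 g difference if the SD is 409.7 g; power is about 73% with 10 and 68% with 9 evaluable patients per group. Replace the word guarantee. Say which population the reference SD comes from. If a sensitivity range is added, for example SDs of 450 to 600 g giving about 70% down to 46% at 11 per group, label it as an assumption.

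This is a change of wording only. It needs no change to conduct while recruitment is under way. The cost is a slightly less favourable stated power.
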